## Abstract

**Background:**

Developing low-cost, socio-culturally appropriate, and scalable interventions for youth depression and anxiety symptoms in low-income regions such as countries in sub-Saharan Africa is a global mental health priority. We developed and intend to evaluate one such intervention for adolescent depression and anxiety in Kenya. The intervention, named Shamiri (a Swahili word for “thrive”), draws upon evidence-based components of brief interventions that involve nonclinical principles rather than treatment of psychopathology (e.g., growth mindset, gratitude, and virtues).

**Methods:**

Four hundred twenty Kenyan adolescents (ages 13–18) with clinically elevated depression and/or anxiety symptoms will be randomized to either the 4-week Shamiri group intervention or a group study-skills control intervention of equal duration and dosage. Participating adolescents will meet in groups of 8–15, led by a high-school graduate trained to deliver Shamiri as a lay-provider. Adolescents will self-report primary outcome measures (depression—measured by the PHQ-8, and anxiety symptoms—measured by the GAD-7) and secondary outcome measures (perceived social support, perceived academic control, self-reported optimism and happiness, loneliness, and academic grades) at the 2-week intervention midpoint, 4-week post-intervention endpoint, and 2-week post-intervention follow-up. We predict that adolescents in the Shamiri group, when compared to the study-skills control group, will show greater improvements in primary outcomes and secondary outcomes.

**Discussion:**

Results may suggest that a brief, lay-provider delivered, school-based intervention may reduce depression and anxiety symptoms, improving academic outcomes and other psychosocial outcomes in adolescents with clinically-elevated symptoms in sub-Saharan Africa.

**Trial registration:**

Pan African Clinical Trials Registry PACTR201906525818462. Registered on 12 June 2019.

## Background

Developing low-cost and scalable interventions for youth depression and anxiety in low-income regions such as countries in sub-Saharan Africa is presently a critical priority of global mental health research [1]. The need for such interventions is warranted because while the incidence of youth depression and anxiety is on the rise, less than half of youths with depression and anxiety symptoms receive needed care [2]. In low-income regions, the burden of youth depression and anxiety is further compounded by limited treatment options [3], social stigma that prevents help-seeking [4], and government under-investment in mental healthcare resources [3, 5]. In addition, the socioeconomic stress associated with poverty (i.e., exposure to violence, inadequate access to basic needs) makes individuals in low-income communities more susceptible to developing psychological disorders [6]. As a majority of psychological disorders begin during adolescence and influence future life outcomes [3], the need for accessible interventions for youths in sub-Saharan Africa cannot be overstated. Here, we detail a protocol for a randomized controlled trial of one such intervention with high-symptom youths in Kenya.

The limited attempts at developing interventions for youth depression and anxiety in sub-Saharan Africa have focused on high-risk youths and have been derived fully or partially from formal psychotherapy interventions for mental disorders [7]. These previous interventions have included elements of cognitive behavioral therapy [8, 9] or adaptations of Western protocols such as the interpersonal therapy for adolescents (IPT-A) [10]. This approach to developing youth mental health interventions in low-income regions poses two major limitations: (1) proper delivery of interventions grounded on traditional cognitive-behavioral therapy procedures necessitates a need for rigorous training of lay-providers, which poses a barrier to dissemination and scalability, and (2) formal therapy procedures make reference to depression and anxiety, which limits help-seeking because of cultural stigma. Given the stigma associated with mental health problems in low-income countries [4, 11, 12], interventions that use non-pathologizing and non-stigmatizing language may be especially useful. As such, interventions that can circumvent both rigorous provider training and cultural stigma might be particularly useful. One such intervention is the Shamiri (“thrive” in Swahili) group intervention for youth depression and anxiety that is delivered by lay-providers in school settings [13].

The Shamiri intervention draws upon evidence-based components of brief scalable interventions that involve non-clinical psychological principles (rather than treatment of psychopathology). Specifically, Shamiri draws on previous research on brief single-component interventions that are sometimes called “wise interventions” [14, 15], some of which have been found to improve youth mental health outcomes [16]. Wise interventions (WIs) are brief and require minimal training of lay-providers. Furthermore, they emphasize overall human functioning rather than referring to mental health disorders. Thus, wise interventions may circumvent social stigma in a way that formal psychotherapy techniques do not [16]. The specific WI components of the Shamiri protocol are growth-mindset [17–19], gratitude [20], and value affirmations [21]. The Shamiri intervention has been trialed previously with Kenyan youths. In a randomized controlled trial of the group-based Shamiri with high-symptom youths in an urban slum (*N* = 51, ages 14–17), adolescents who met a clinical cut-off for depression and anxiety were randomized into either the Shamiri intervention or an active study-skills control group; those assigned to the intervention group showed improvements in youth depression and anxiety symptoms, academic performance, and perceived social support from friends [13]. However, the trial was limited by a modest sample size and limited follow-up. Consequently, a replication of the Shamiri intervention with larger sample size is a logical next step.

This study has two primary objectives. The first is to evaluate an enhanced Shamiri group intervention—which incorporates student and stakeholder feedback from the previous Shamiri trial [13]—for depression and anxiety for youths with elevated symptoms in Kenya. The Shamiri intervention aims to be low-cost, to be positively focused in order to circumvent stigma, and will rely on empirically supported principles that can be delivered in a low-resource community setting by lay-providers. The second objective is to conduct moderator and mediator analyses on study outcomes to identify for whom and under what circumstances the treatment works.

The present study’s primary outcomes are youth depressive and anxiety symptoms. The secondary outcomes are social support, perceived control, gratitude, loneliness, emotional regulation, and academic outcomes. We predict that youths assigned to the Shamiri intervention will experience reductions in primary outcome measures and improvements in secondary outcomes measures when compared to youths assigned to an active “study-skills” control group from baseline to post-intervention endpoint. We opted for an active study-skills control group because we wanted all participants to have an opportunity to benefit from participation [13] and because a recent meta-analysis of youth psychotherapy indicated that active control conditions provide a more rigorous standard of comparison as opposed to passive controls such as a waitlist [22]. Including a control condition comparable in dose and intensity to the treatment condition also helped to ensure that any condition difference in study outcomes could be attributable to intervention content rather than differences in dose or intensity of the two study conditions.

## Methods

### Study design

#### Trial design

The trial is a randomized controlled trial with two arms: the Shamiri intervention and a study-skills control intervention. The intervention and control conditions are described in detail later and summarized in Table 1. Interventions will be delivered in schools to groups of 10–13 youths by high school graduates trained to be lay-providers. Assessments will be administered at initial screening, 2-week midpoint, 4-week endpoint, and 2-weeks post endpoint. Academic performance data on grades and national exams will be collected for the school-term before, during, and after study participation. Any data required to support the protocol will be publicly available in an online repository [10.17605/OSF.IO/KTW25] or upon request.

**Table 1 Tab1:** Arms of the Shamiri randomized control trial

Study arm	Content	Delivery
Shamiri intervention	Consists of four sessions made up of three modules: growth-mindset (two sessions), gratitude (one session), and virtues (one session).	High school graduates trained as lay-provider (“group leader”). One group leader will be assigned to each group of 10–13 youths.
Study-skills control	Consists of four sessions with content that focus on study skills. Specific modules will include note-taking, effective study strategies, tips for time management, and the study cycle. Equal dose and duration as Shamiri intervention.	High school graduates trained as lay-providers (“group leader”). One group leader will be assigned to each group of 10–13 youths.

#### Study setting

This study will take place in four secondary schools located in Nairobi and neighboring Kiambu Counties, Kenya. Nairobi County is one of 47 geographical counties that act as units of devolved government in Kenya, a low-income country in sub-Saharan Africa. Nairobi is a diverse city with a population of at least 3.2 million that is representative of the cultural and socioeconomic diversity in Kenya [23]. Kiambu County, a county that is part of the former Central Province region, neighbors Nairobi County and has a population of at least 1.7 million [23]. The first author will draw a list of public secondary schools in Nairobi and Kiambu counties. Principals of the schools will be contacted with information about the study and asked to enlist their school to participate. From the pool of interested schools, four schools that have strong demographic, socioeconomic, and educational diversity will be selected. In particular, the selection will be done in such a manner that schools that are ranked as national secondary schools (which have a socio-economically diverse student body from all the regions in Kenya) and sub-county secondary schools (which are often resource-poor day single-sex or mixed secondary schools with student body from the local area) by the Ministry of Education, Science and Technology will be selected—more information on the diversity of secondary schools in Nairobi and Kiambu counties can be seen elsewhere [24, 25]. In total, the final school sample will consist of an all-boys *national* boarding secondary school, an all-girls *national* boarding secondary school, an all-girls *sub-county* day secondary school, and a *sub-county* mixed-day secondary school. This diverse and generalizable sample of high-symptom youth in Kenya will also allow us to conduct robust moderator analyses that can allow us to identify for whom the Shamiri intervention works for.

As reported elsewhere [13], the Shamiri intervention was designed through close multicultural collaboration by experts from Kenyan and American institutions (the first author, for example, is a Kenyan citizen who went through the Kenyan public education system and brings firsthand experience of the same). Kenyan stakeholders (school administrators, students, and community members) were also extensively involved in the intervention development and adaptation process to ensure that the intervention was socio-culturally appropriate for the Kenyan context [13]. Such multicultural collaboration is particularly necessary for global mental health research [26].

### Procedures

#### Participant recruitment and screening

In all four participating schools, students in Form One, Form Two, and Form Three (and in smaller schools Form Four) will be notified about the study by the school principals and other administrators. All students aged between 13 and 18, inclusive, will be eligible for the study if they self-report either elevated depression symptoms or elevated anxiety symptoms—indexed by a score of 15 or higher on the Patient Health Questionnaire (PHQ)-8 (indicating moderate or severe depression) or a score of 10 or greater on the GAD-7 (indicating moderate or severe anxiety) [27, 28]. No other exclusion criteria will be applied. Of eligible students, approximately 140–180 will be randomly selected at each school to participate in the study. See the “Randomization, treatment allocation, and blinding” section for more information on selection and randomization.

Students will complete a questionnaire battery to determine study eligibility. To control for ordering effects, scales in the questionnaires will be presented in different orders. Parental consent will be sought for all minor participants. As the schools in which we will be conducting study activities are boarding schools, many of the students will not have direct access to their parents [24, 25]. Additionally, because of the logistical difficulties of the study team obtaining written consent from parents who live in many different parts of the country—many quite distant from the schools and not readily accessible—the Ethics Review Committee at MUERC determined that school principals and other administrators would seek parental/guardian permission from parents of the students interested in the study using their locally available policies and resources—for example, a school in Nairobi county with students from all the geographical counties in Kenya may call or write parents/guardians—per MUERC guidelines. This process was used in the pilot study [13] and has been used in multiple studies with Kenyan adolescents [24, 25, 29]. Only students for which parental permission will be obtained through this process will be allowed to participate in the study. School administrators will then gather these students in classrooms or school halls where they will meet the study team. Here, the study team will further inform them about the study and that their participation is voluntary and that they can opt out. After being provided with an opportunity to ask questions, they will provide informed consent if they wish to participate. Only participants for whom informed consent or informed assent and parental consent (in the case adolescent minors) is received will be allowed to participate. The study team and a school administrator will witness the process of obtaining informed consent. On the consent form, participants will be asked if they agree to the use of their data should they choose to withdraw from the trial. Participants will also be asked for permission for the research team to share relevant data with people from the Universities taking part in the research or from regulatory authorities, where relevant. This trial does not involve collecting biological specimens for storage. There is no anticipated harm for trial participation and there is no provision for post-trial care. See Fig. 1 for a participant flowchart.

**Fig. 1 Fig1:**
[figure not shown]
CONSORT flow diagram

#### Randomization, treatment allocation, and blinding

Following baseline assessment and recruitment, youths who meet the inclusion criteria will be randomly allocated within each school to the Shamiri intervention or the study-skills control condition using a computerized random number generator in R Studio. We will use stratified randomization to ensure consistent baseline characteristics (age, form, and sex if mixed school) across groups. There will be no special criteria for discontinuing or modifying allocated interventions. Participants and group leaders will not be blinded to treatment allocation. However, they will not be informed of study hypotheses. To control for possible contamination, the study will be presented to all eligible students as a Wellness and Academic Functioning Program that was intended to improve both academic functioning and wellness. Both conditions will also be of equal duration and will require similar efforts, and group leaders will be instructed to collect study materials at the end of each session (to prevent students from noticing differences in their program materials and learning from others’ materials during the study).

#### Group leader selection and training

Both the Shamiri and study-skills groups will be led by trained group leaders who will serve as lay-providers. To qualify as a group leader, an individual must be a Kenyan high school graduate between the ages of 17 and 26, inclusive, and he or she must live in the local community in and around Nairobi. While most group leaders will be either planning to matriculate or already attending a local university in Nairobi, neither college admittance nor attendance is a requirement for consideration. The above group leader characteristics are important for the successful implementation of this protocol for several reasons: (1) Local group leaders’ understanding of the culture, language, and local customs in schools make them better-positioned to deliver the intervention than outsiders. (2) Group leaders who are closer in age to the youths in the program may be better positioned than older adults to connect with youths—this is because Kenyan cultural norms around age relations dictate that youths should primarily listen rather than speak in the company of adults. (3) Lastly, this model is potentially scalable: given that the mean age in Kenya is 19, there is a large pool of youths aged 17–25 from which group leaders could be selected—median age is 19 [30].

We will recruit group leaders through advertisements in high school graduate platforms on various media such as WhatsApp and Facebook. We will also recruit through local universities and organizations in Kenya that work with high school graduates. All interested group leaders will be offered an opportunity to express their interest via a brief online form. Group leaders who meet the above-specified criteria will be invited for a 25-min interview with members of the study team. This interview will assess past teaching experiences, interest in the project, familiarity with mental health and wellness issues, and interpersonal facilitation skills. Chosen group leaders will then be contacted via email and phone and invited to a mandatory 10-h training. Due to funding constraints, we intend to recruit 12 group leaders. All group leaders will be compensated $150 plus the cost of transportation for the entire duration of the study.

The group leader training, which will be conducted by members of the research team, will begin with 4 h of general communication and group leadership skills such as active listening, noting connections between group members, handling conflicts within the groups, and referring students in need to appropriate school officials if necessary. Group leaders will then be trained didactically in the specific content of each week of the interventions. All group leaders will receive detailed and structured outlines of the content of each intervention and control session. The outlines will include sample wording for the group leaders. The last six of the 10 h of training will consist of role-plays in which the leaders practice leading groups in portions of the protocol. Following the role-plays, leaders receive feedback from their fellow group leaders and from the study team. The leaders are then asked in the full group setting to reflect on their experiences and learnings from the role-plays. A detailed protocol for the recruitment and training of group leaders is available elsewhere [30].

Upon completion of training, group leaders will be randomly assigned to lead either Shamiri intervention or control groups. Given that we will have about 48 groups of up to 15 youths in the entire study, group leaders will be randomly assigned to either the intervention or control condition at each school. That is, the randomization process will be repeated for each distinct school. For instance, one group leader might lead a study-skills control group in School A but a Shamiri intervention group in School B. This randomization should allow us to account for group leader differences in competence and leadership style. However, group leaders will be instructed to strictly follow the protocol manual for the condition that they will be leading and not use content from the other condition during their sessions. Student composition in the groups will reflect the composition of the school. In a single-sex school, all groups will be single-sex.

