#### Data description: nesting, missingness, and imputation

There will be four levels of clustering in our data: school (level 4), group-leader (level 3), groups (level 2), and participant (level 1) with repeated measures being the individual observations at the multiple timepoints (level 0). Group leaders and schools will be cross-classified in an unstructured manner as group leaders will be able to lead groups in multiple schools. Groups will be strictly nested within group leaders as participants will be within groups (structured cross-classification). Missing item (measurement) and subject-level data will be imputed twenty times using Fully Conditional Specification (FCS), implemented using the multivariate imputation by chained equations (mice) algorithm in R as described by Buuren and Groothuis-Oudshoorn [49].

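### Randomising leaders to condition separately at each school, with no stated balance across schools, gives up some precision that a restricted two-and-two assignment would keep

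*Protocol article*

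**What the plan says.** The protocol article, under Group leader selection and training, gives the rule: "group leaders will be randomly assigned to either the intervention or control condition at each school", and "the randomization process will be repeated for each distinct school". Its one example is a leader who runs a control group in one school and a Shamiri group in another. The stated purpose is that "This randomization should allow us to account for group leader differences in competence and leadership style". The same section says that "we intend to recruit 12 group leaders".

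Under Data description: nesting, missingness, and imputation, it adds: "Group leaders and schools will be cross-classified in an unstructured manner as group leaders will be able to lead groups in multiple schools". The analysis section models leaders and schools as crossed random effects and tests condition by time. It names random slopes for individuals and, in one of two candidate models, for schools, but none for leaders.

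No sentence requires a leader to serve both arms. None says that the draws are unrestricted across schools either.

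**The concern.** The scheme is meant to deal with differences between leaders. It does this best when each leader serves both arms equally, because the leader's own skill then drops out of the comparison. Separate draws at each school do not guarantee that. A leader can land in the same arm every time, or three times out of four, and part of the treatment contrast then rests on comparing different leaders. A random leader effect in the model can weight that part correctly, but it cannot supply a within-leader comparison that the assignment did not create.

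At stake is the width of the confidence interval for both primary outcomes. The sample size was calculated with no allowance for covariates or clustering, so it contains no stated margin for such a loss.

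**Working it through.** The protocol gives no figure for leader balance or for information lost, so there is nothing of its own to reproduce on this point.

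**Inputs from the protocol article**
- 12 leaders (Group leader selection and training).
- "we will have about 48 groups of up to 15 youths in the entire study" (same section).
- "This study will take place in four secondary schools located in Nairobi and neighboring Kiambu Counties, Kenya" (Study setting).
- Target of 420 participants and d = .3 at alpha .05 (Sample size and statistical power).

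**Assumptions, not in the protocol**
- One group per leader per school: 48/4 = 12 groups per school, and 48/12 = 4 groups per leader.
- Six leaders per arm in each school, with draws independent across schools.
- Group size m = 420/48 = 8.75, total variance 1, group variance sG = .02, and leader ICC sL = .01, .03 or .05.
- School effects fixed, variance components known, two-sided test.

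**1. How leaders split.** For one leader over four schools:
- same arm in all four: 2 × (1/2)^4 = 12.5%
- three to one: 8/16 = 50%
- two and two: 6/16 = 37.5%

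The expected number of one-arm leaders is 12 × .125 = 1.5. In 20,000 simulated assignments the mean was 1.50. The chance of at least one such leader was 78%, and of at least two 46%. As a hand check, treating leaders as independent gives 1 − .875^12 = 80%; the six-to-six restriction lowers this slightly.

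**2. Share of the contrast that lies between leaders.** Code the arms +1 and −1, and let S be a leader's sum over four groups. The mean of S² is .125 × 16 + .5 × 4 + .375 × 0 = 4. The between-leader sum of squares averages 12 × 4/4 = 12 out of 48, a share of .25. In a two-and-two layout S = 0 for every leader and the share is 0.

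**3. Information lost against two-and-two.** Average loss = .25 × 4sL/(4sL + v), with v = sG + (1 − sL − sG)/m.

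| sL | v | 4sL/(4sL + v) | average information loss | mean rise in variance | rise exceeded in the worst 5% of draws |
|---|---|---|---|---|---|
| .01 | .1309 | .04/.1709 = .234 | 5.9% | 6% | 11% |
| .03 | .1286 | .12/.2486 = .483 | 12.1% | 14% | 25% |
| .05 | .1263 | .20/.3263 = .613 | 15.3% | 19% | 34% |

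The last two columns come from simulated draws. Putting the average loss into 1/(1 − loss) − 1 gives 6.2%, 13.7% and 18.1%; averaging over draws gives slightly more.

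**4. Range.** At sL = 0 the loss is 0. As sL grows large relative to v, it tends to 25%. With group variance 0, leader ICCs of .01 to .05 give 6.5 to 16.2% at m = 8.75, and 9.4 to 19.0% at m = 15.

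**5. Power at d = .30.** Under two-and-two the variance of the arm difference is 4v/48 = v/12, and power is about 82%, 83% and 83% at the three ICCs. Under separate draws, mean power is about 80%, 77% and 77%.

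**6. The planned condition-by-time test.** Steps 3 to 5 treat a single analysed value per youth. In the repeated-measures model, a leader random intercept alone gives a loss of exactly 0, because it cancels within participants. With a leader-by-time variance of .02 or .05 (total variance 1, groups of 9), the average information loss is 9.8% or 15.7%.

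**7. Does a balanced layout exist?** There are six ways to choose two of four schools. Using each twice covers 12 leaders. Each school appears in three of the six patterns, so it has 3 × 2 = 6 Shamiri leaders and 6 control leaders.

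**The case against.** The strongest objection is step 6: the planned test is condition by time, and the only leader term clearly named cancels from it. That stands as a condition on the finding, because precision is lost only if leaders differ in their effect on change. It does not dispose of the point. Youths are allocated after the baseline assessment, so leaders cannot have affected baseline scores, and any leader effect must act on change. If the model has no leader variation in change, imbalance adds variance that the model does not show. With equal groups, a two-and-two layout cancels additive leader effects on change whether or not they are modelled.

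Other objections also stand in part:
- The leader ICC is unknown, and 12 leaders by themselves say nothing about how much leaders vary.
- The protocol says that leaders will be able to work in several schools, not that each works in all four. The count of 48 groups is approximate, and 420 youths in groups of 10 to 13 would make only 32 to 42 groups.
- The power cost is modest. At the 140 to 180 youths per school given under Participant recruitment and screening (11.7 to 15 per group over 48 groups), the same model leaves 85 to 93% power after the loss.
- The text does not rule out a restriction across schools.

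A reader might infer that leader skill is confounded with condition and biases the result. The protocol does not support that: leaders are randomised within each school, youths are randomised within each school, and leaders are in the model. About 10.5 of 12 leaders would still serve both arms, so the stated purpose is largely met.

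**Conclusion.** The point holds as a cheap improvement of minor severity. As described, the scheme does not ensure that each leader serves both arms. One-arm leaders are likely but not certain: about 22% of draws would contain none.

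The cost is precision only, and its size is conditional. It rests on leaders differing in their effect on change, on assumed leader ICCs, and on one group per leader per school. A reader might take 6 to 19% as a settled share of information lost. Under the main settings that range is the rise in variance, and the matching share of information is about 6 to 15%. Nothing in the protocol fixes either figure within the wider range of 0 to 25%. Under the assumed layout, the two-and-two assignment is never less efficient.

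**What to change.** Restrict the leader randomisation across schools. Where the roster allows, each leader leads Shamiri in two schools and study-skills in the other two, with six leaders per arm in each school. One way is to use each of the six two-of-four school patterns twice and assign patterns to leaders at random. Keep the leader term in the model, and state the leader ICC assumed when judging precision.

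The cost is planning. The assignment must be drawn for all four schools in advance, and exact balance depends on each leader working in every school; otherwise the aim is the closest balance that the roster permits.

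The Trial status section lists the trial as completed, so the layout change serves a later trial. For this one, the report can tabulate the realised leader-by-condition assignment and allow for leader variation in change.
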